# The effects of sodium butyrate supplementation on the expression levels of PGC-1α, PPARα, and UCP-1 genes, serum level of GLP-1, metabolic parameters, and anthropometric indices in obese individuals on weight loss diet: a study protocol for a triple-blind, randomized, placebo-controlled clinical trial

**DOI:** 10.1186/s13063-022-06891-9

**Published:** 2023-08-01

**Keywords:** Sodium butyrate, Obesity, Energy metabolism genes, Appetite, Randomized controlled trial

## Abstract

**Background:**

*Obesity* is a multifaceted disease characterized by an abnormal accumulation of adipose tissue. Growing evidence has proposed microbiota-derived metabolites as a potential factor in the pathophysiology of obesity and related metabolic conditions over the last decade. As one of the essential metabolites, butyrate affects several host cellular mechanisms related to appetite sensations and weight control. However, the effects of butyrate on obesity in humans have yet to be studied. Thus, the present study was aimed to evaluate the effects of sodium butyrate (SB) supplementation on the expression levels of peroxisome proliferator activated-receptor (PPAR) gamma coactivator-1α (PGC-1α), PPARα and uncoupling protein 1 (UCP1) genes, serum level of glucagon-like peptide (GLP1), and metabolic parameters, as well as anthropometric indices in obese individuals on a weight loss diet.

**Methods:**

This triple-blind randomized controlled trial (RCT) will include 50 eligible obese subjects aged between 18 and 60 years. Participants will be randomly assigned into two groups: 8 weeks of SB (600 mg/day) + hypo-caloric diet or placebo (600 mg/day) + hypo-caloric diet. At weeks 0 and 8, distinct objectives will be pursued: (1) PGC-1α, PPARα, and UCP1 genes expression will be evaluated by real-time polymerase chain reaction; (2) biochemical parameters will be assayed using enzymatic methods; and (3) insulin and GLP1 serum level will be assessed by enzyme-linked immunosorbent assay kit.

**Discussion:**

New evidence from this trial may help fill the knowledge gap in this realm and facilitate multi-center clinical trials with a substantially larger sample size.

**Trial registration:**

Iranian Registry of Clinical Trials: IRCT20190303042905N2. Registered on 31 January 2021.

## Introduction

Obesity is caused by a positive energy imbalance when energy consumed exceeds energy expenditure [1]. Obesity plays a crucial role in the genesis of many chronic disorders, including cardiovascular disease, type 2 diabetes mellitus (T2DM), rheumatoid arthritis, and various cancers, causing complications such as glucose intolerance, insulin resistance (IR), systemic inflammation, hyperlipidemia, and hypertension [2, 3]. The World Health Organization (WHO) estimates that the global prevalence of obesity has tripled since 1975 [4]. If current trends continue, by 2025, there will be 2.7 billion overweight people and more than 1 billion obese people [4]. This demonstrates that obesity has steadily increased over the last few decades and is now a global health concern [1].

Obesity is a multifactorial disease in which, in addition to heredity, environmental, social, physiological, and metabolic factors all play an essential role in its occurrence [5]. The appetite of obese people usually increases, while their energy expenditure decreases, owing to insufficient physical activity and brown adipose tissue (BAT) dysfunction [6].

BAT contributes significantly to energy expenditure by burning triglycerides (TG) and glucose in humans [7]. In recent years, researches on the relation of intestinal microbiota with obesity and epigenetic modifications have remarkably grown. The metabolic functions of the intestinal microbiota are the fermentation of dietary fiber and the production of short-chain fatty acids (SCFAs) [8]. In the lumen of the colon, the significant SCFAs are acetate (C2), propionate (C3), and butyrate (C4) in a 1:1:3 molar ratios. Increased bacterial fermentation of SCFAs contributes to the regulation of systemic energy by reducing hepatic production of glucose and lipids [9, 10].

Animal models of metabolic diseases have reported that among all SCFAs, butyrate has the highest anti-obesity activity [11]. There are several mechanisms through which butyrate works, including preventing weight gain caused by a high-fat diet (HFD), reducing serum TG, total cholesterol, glucose, IR, and improving hepatic steatosis [11, 12]. Firmicutes and Bacteroides are the two main types of butyrate-producing bacteria; previous research has shown that these bacteria are reduced in the obese people [13]. On the other hand, a study showed that the butyrate-producing bacteria are higher in lean people, and when these bacteria are transferred to the intestines of people with metabolic syndrome (MetS), their IR status improves [14].

Treatment of obesity and obesity-related disturbances depends mainly on diet, exercise, and drugs to treat specific components, such as orlistat, metformin, and statins [15, 16]. This pharmaceutical strategy can lead to drug interactions, as people with MetS may require several medications [17]. Additionally, treating one component of MetS can harm another [15]. In this regard, butyrate, a microbial metabolite, has recently sparked much interest as a safe supplement that could decrease weight, serum glucose, cholesterol, and blood pressure while having minimal side effects [11, 12, 18]. Butyrate, a histone deacetylase inhibitor, could hyper-acetylate transcription factors and change several genes expression level especially peroxisome proliferator activated-receptor (PPAR) gamma coactivator-1α (PGC-1α), PPARα, and uncoupling protein 1 (UCP1) [19, 20]. Furthermore, butyrate stimulates the secretion of some gastrointestinal anorexic hormones, including the glucagon-like peptide (GLP-1) [21].

Overall, evidence from in vivo and in vitro studies showed that butyrate has a remarkable impact on metabolic regulation and body composition [11]. Butyrate has been strongly linked to increased energy expenditure, fatty acid oxidation, and decreased energy intake. Therefore, it appears that butyrate can be considered a potential therapeutic agent for obesity and MetS. Hence, due to eminent anti-obesity effects of butyrate as well as lack of human clinical trials to evaluate the effects of butyrate in obesity, the present study was aimed to investigate the effects of sodium butyrate (SB) supplementation on the expression levels of PGC-1α, PPARα, and UCP1 genes, serum level of GLP-1, metabolic parameters, and anthropometric indices in obese individuals.

## Methods

### Study design and setting

A triple-blind, parallel-group, single-center and superiority placebo-controlled clinical trial with 1:1 allocation ratio will be conducted. The proposed RCT will take place in the Faculty of Nutrition and Food Sciences, Tabriz University of Medical Sciences, for 8 weeks to see how daily 600 mg SB supplementation affects obese people.

Individuals will be recruited for clinical trial through widely distributed printed and social media advertisements from the health centers of Tabriz University of Medical Sciences (including hospitals, outpatient receptions, communities, and health clinics). Initial screening and enrollment will be done by a nutritionist. Screening will continue until the target sample size is achieved. Interpretation of laboratory results, analysis of body composition, and dietary intakes will be performed for individuals without charge as incentives. Figure 1 depicts the study flow chart.

**Fig. 1 Fig1:**
[figure not shown]
Study flow chart

### Participants

The study will involve 50 obese individuals. Participants will be both male and female aged 18 to 60 years old, with body mass index (BMI) of 30 to 40 kg/m^2^; non-inclusion criteria will be included: lack of interest in continuing the study; having diabetes, kidney diseases, heart failure, rheumatic diseases, cancers, liver failure, gastrointestinal disorders; history of obesity surgery; following a weight loss diet or taking any supplements or weight loss drugs in the last 6 months; smoking; and pregnancy, lactation, or menopause.

### Registries and ethics

Eligible participants will receive the study protocol and will then be able to have an informed discussion with the participating consultant. Trained researcher will obtain written consent from patients willing to participate in the trial. Consent forms will be provided for all parents involved in the trial. A material consent form will be taken for extra biological samples (serum, plasma, and stool) which will be used in future studies. If the data collection in the ancillary study is not included in the informed consent process of main RCT, participants should provide written consent.

This protocol was approved by Ethics Committee of Ahvaz Jundishapur University of Medical Sciences (approval number: IR.AJUMS.REC.1399.845). The research was also registered at the Iranian Registry of Clinical Trials (IRCT20190303042905N2). The protocol must be amended if any changes can affect the conduct of the study, the participant benefits, or supplement use safety, including a change in study objectives, study design, procedures, sample size, or significant administrative changes. It will be agreed upon by IRCT and approved by the Ethics Committee before implementation. The participant’s information will be kept in the lockers in restricted areas. Data collection forms and biological samples will be given a unique code in order to ensure confidentiality.

### Sample size

The sample size was estimated based on serum changes of GLP-1 [22], 95% confidence interval, and 80% power (two-sided *α* = 0.05 and *β* = 0.2) using sample size formula (Fig. 2) suggested for comparison of mean between the two groups when the endpoint is quantitative data in parallel designed RCTs. Furthermore, the means and standard deviation (SD) [23] of GLP-1 levels in the study mentioned above were as follows: Δμ = 17.84; SD1 = 17.93; and SD2 = 22.49. Lastly, considering a 20% dropout rate, 25 subjects were calculated for each group. Individuals who fulfilled the eligibility criteria will be included in the RCT.

**Fig. 2 Fig2:**
[figure not shown]
Sample size calculating formula. *α* is the significance level, *β* is the power of the test, *δ* is standard deviation, and μ1_μ2 is difference between the means

### Blinding and randomization of participants

All participants will be randomly assigned into two groups (intervention or placebo), stratified by age (two age groups: 18–39 years and 40–60 years) and gender (male and female). The intervention group will receive SB supplementation + hypo-caloric diet (*n* = 25), and the placebo group will receive placebo capsule + hypo-caloric diet (*n* = 25). The random block design will be performed by a third person using the Random Allocation Software (RAS). After the baseline evaluations, and checking the inclusion and exclusion criteria by two of the main researchers, eligible person will be allocated into the intervention or control groups using sealed envelopes.

In case of emergency, where it is essential to be aware of the treatment allocation. The clinical consultant who is not involved in the enrolment and intervention process will have access to the unblinding envelopes provided for every individual. Further evaluation and required medical intervention will be done depend on situation. The reason of emergency unblinding will be recorded in the case report form and revealed treatment code will not be recorded in the study documents or verbally disclosed to the researchers or participants.

Random numbers will be labeled as SB or placebo bottles, and even or odd numbers will be randomly assigned to the study groups. To maintain blindness, instead of A or B, the third person will use specific codes. The bottles will be similar in appearance and weight to achieve blinding. The treatment allocation will be concealed from participants, researchers, and outcome assessors.

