### Statistical analysis

Data analysis of the present RCT will be conducted on an intention to treat (ITT) participants. ITT means outcome data obtained from all participants are included in the data analysis, regardless of protocol adherence. The data will be checked for accuracy and completeness at random intervals. The data will be expressed as means ± SD. For each variable, the percentage change will be calculated, as follows: [(E–B)/B ×100]; *E* is the end value, and *B* is the baseline value of the variable.

The Kolmogorov-Smirnov test will be used to examine the normality of the data. The intervention arm (SB) will be compared against the control (placebo) for all primary and secondary outcomes. The paired sample *t*-test and independent sample *t*-test will be performed for the comparison of parametric variables within and between groups, respectively. For non-parametric variables, the Mann-Whitney test and Wilcoxon signed rank test will be applied. Confounding factors including baseline values will be controlled using the analysis of covariance (ANCOVA) test. IBM SPSS software (version 21) (Armonk, NY, USA) will be used to analyze the data. A *P*-value less than 0.05 will be considered a statistically significant.

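### Randomisation is stratified by age group and sex, but the named between-arm tests ignore both and the ANCOVA does not commit to them, which may forgo precision.

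*Protocol article*

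**What the plan says.** Under Blinding and randomization of participants, allocation is "stratified by age (two age groups: 18–39 years and 40–60 years) and gender (male and female"), which gives four strata. It is blocked: "The random block design will be performed by a third person using the Random Allocation Software (RAS"). No block size is given.

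The Statistical analysis section names the comparisons for all primary and secondary outcomes. For normally distributed variables, the paired and "independent sample *t*-test will be performed for the comparison of parametric variables within and between groups, respectively". Otherwise, "For non-parametric variables, the Mann-Whitney test and Wilcoxon signed rank test will be applied". One further sentence covers adjustment: "Confounding factors including baseline values will be controlled using the analysis of covariance (ANCOVA) test". Baseline values are the only covariates named. The section does not say whether the t-test or the ANCOVA is the main analysis.

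The Sample size section rests on an unadjusted comparison of two means for GLP-1: "80% power (two-sided *α* = 0.05 and *β* = 0.2"), with "Δμ = 17.84; SD1 = 17.93; and SD2 = 22.49".

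**The concern.** Blocking within strata balances age group and sex between the arms, so differences between strata largely drop out of the true sampling variation of the arm difference. A plain t-test does not use this. It leaves the between-stratum variation in its error term. If age group or sex predicts the outcome, the reported standard error exceeds the true one, the confidence interval is too wide and the test rejects less often than 5% under the null hypothesis. The Mann-Whitney test also disregards the strata.

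Precision that the design has already secured may therefore be lost in a trial of 50 people. The ANCOVA could recover it, but the text does not say that it will. The open covariate list has a second consequence: nothing limits it to variables measured before randomisation. The trial records diet and appetite at the end of the study, and the Introduction links butyrate to lower energy intake. Adjusting for such a variable could remove part of the effect under study.

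**Working it through.** **Inputs from the protocol article.** Difference 17.84, SDs 17.93 and 22.49, two-sided α 0.05, 80% power, 20% dropout and 25 per arm (Sample size); four strata and blocked allocation (Blinding and randomization of participants).

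**Step 1: reproduce the sample size.**
- Pooled SD = √[(17.93² + 22.49²)/2] = 20.34.
- n per arm = 2 × [20.34 × (1.96 + 0.8416)/17.84]² = 20.40.
- With the 20% allowance, 20.40 × 1.2 = 24.5, rounded up to 25. This matches "considering a 20% dropout rate, 25 subjects were calculated for each group".

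The SDs carry no covariate adjustment, so the planned power is that of an unadjusted comparison. With 25 × 0.8 = 20 completers per arm, it is 79% by the normal approximation and 77% by the t distribution.

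**Step 2: expected size of the effect.** Let R² be the share of outcome variance explained by age group and sex.
- Unadjusted standard error at 20 per arm: 20.34 × √(2/20) = 6.43.
- With the strata in the model it is about 6.43 × √(1 − R²): 6.10 at R² = 0.10, 5.75 at 0.20 and 5.38 at 0.30.

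**Step 3: simulation.** There were 5,000 trials per setting, with N = 50, allocation blocked within the four strata and 20% random dropout. An unadjusted t-test was compared with a linear model that adds age group and sex. These assumptions are not in the documents: blocks of 4, 30% of participants in one sex, an even age split, a common SD of 20.34, R² shared equally between the two factors, and R² itself. Power is at the difference of 17.84.

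| Assumed R² | Power, unadjusted | Power, adjusted | Mean SE, unadjusted | Mean SE, adjusted | Type I error, unadjusted | Type I error, adjusted |
|---|---|---|---|---|---|---|
| 0 | 76.3% | 75.0% | 6.40 | 6.45 | 5.1% | 5.0% |
| 0.05 | 78.3% | 79.4% | 6.43 | 6.32 | 4.5% | 5.0% |
| 0.10 | 76.6% | 79.3% | 6.45 | 6.16 | 4.0% | 4.9% |
| 0.20 | 78.6% | 84.7% | 6.43 | 5.77 | 3.8% | 5.3% |
| 0.30 | 78.9% | 88.2% | 6.46 | 5.42 | 2.4% | 4.9% |
| 0.40 | 80.3% | 93.6% | 6.47 | 5.02 | 2.4% | 5.3% |

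Monte Carlo error is about 0.6 points on power, from √(0.78 × 0.22/5,000), and 0.3 points on type I error, from √(0.05 × 0.95/5,000). The adjusted standard errors are close to those in Step 2.

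The conservatism shows directly in the null runs. At R² = 0.20 the unadjusted estimate actually varied with an SD of 6.06, while the t-test reported a mean standard error of 6.43. At R² = 0.30 the figures were 5.70 and 6.43.

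**What was not computed.** The gain from adding the strata to an ANCOVA that already contains baseline was not simulated, nor was the Mann-Whitney test.

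**The case against.** The strongest objection is that the protocol does plan an ANCOVA. Its covariate list is open, age and sex are natural members of it, and a journal article commonly leaves the exact list to an analysis plan. Part of this stands. A reader might infer that age and sex are excluded from every planned analysis, and the text does not support that. The objection does not remove the point, because the article names specific unstratified tests for all outcomes and does not say that the ANCOVA takes precedence.

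A second objection is that the loss is conditional, and this stands in full. A reader might infer that the standard errors are certainly too large. The documents give no figure for how well age or sex predicts any outcome. At R² = 0 there is nothing to gain. The outcomes are changes, which age and sex may predict less well than levels, and baseline adjustment may absorb part of any gain.

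A third objection is that nothing invalid follows, and this also stands. A reader might infer that the trial is underpowered as a result, or that type I error is inflated. The 25 per arm was sized on an unadjusted comparison, so leaving out the strata does not take power below that plan, and the error in the test is towards caution.

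Finally, a reader might infer that adjustment for end-of-study intake or appetite is intended. The article names no such covariate. The wording only leaves the possibility open.

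**Conclusion.** The point holds as a mismatch between design and analysis. The strata used in randomisation are absent from the named tests and are not committed to in the ANCOVA. Against an unadjusted t-test, fitting them changes power by about −1 point at an assumed R² of 0, +2 to +3 points at 0.10, +6 at 0.20 and +9 at 0.30. Over the same values, the type I error of the unadjusted test falls from 5.1% to 4.0%, 3.8% and 2.4%.

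These figures rest on about 20 completers per arm, random dropout and the assumed block size and stratum mix. R² is not known from the documents, and the gain over a baseline-adjusted ANCOVA may be smaller. The consequence is forgone efficiency of uncertain size.

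**What to change.** In the Statistical analysis section, state that the main between-arm comparison is an ANCOVA with arm, the baseline value of the outcome, age group (18–39 or 40–60) and sex, and that covariates are limited to variables fixed before randomisation. Keep the t-test or Mann-Whitney test as supportive. For outcomes that fail the normality check, state the scale on which the ANCOVA is fitted. A stratified rank test (van Elteren) is optional: 20 completers per arm over four strata average only 5 per arm in each, and uneven strata would be sparser.

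The cost is a short change of wording and three covariate degrees of freedom, one of them for the baseline value that the plan already names. The two strata terms cost about 1 point of power if age and sex are not prognostic. No new data are needed, because both factors must be known to randomise.

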### Criteria for discontinuing or modifying allocated intervention

Since SB may affect the composition of the gut microbiota, temporary gastrointestinal symptoms such as bloating or diarrhea may occur. Taking the recommended daily dose regularly, gastrointestinal tolerance improves, and the symptoms usually disappear. However, the trial medication should be withdrawn from subjects reporting gastro-intestinal intolerance. This should be reported as an adverse event.

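### Even/odd numbering of bottles ties the label to the arm; if blinded people can see the numbers, one leaked or inferred allocation identifies all the others

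*Protocol article*

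**What the plan says.** The section *Blinding and randomization of participants* of the Protocol article contains the following elements:

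- **List.** Allocation is stratified by two age bands and by gender. A third person prepares random blocks with allocation software.
- **Envelopes.** After the baseline checks, each "eligible person will be allocated into the intervention or control groups using sealed envelopes".
- **Bottles.** "Random numbers will be labeled as SB or placebo bottles", and "even or odd numbers will be randomly assigned to the study groups".
- **Codes.** "To maintain blindness, instead of A or B, the third person will use specific codes".
- **Promise.** "The treatment allocation will be concealed from participants, researchers, and outcome assessors".
- **Emergency unblinding.** A clinical consultant outside enrolment and treatment "will have access to the unblinding envelopes provided for every individual". The "revealed treatment code will not be recorded in the study documents or verbally disclosed to the researchers or participants".

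The section *Criteria for discontinuing or modifying allocated intervention* adds that on SB "temporary gastrointestinal symptoms such as bloating or diarrhea may occur".

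**The concern.** A bottle label should tell a blinded person nothing about which participants share an arm. A parity rule does tell them, because every odd bottle belongs to one arm and every even bottle to the other. Choosing at random which parity means SB hides a single yes/no fact, and that one fact covers the whole trial.

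Two things would be at stake if the numbers were visible:

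- **Blinding.** The primary outcomes (section *Outcomes*) include anthropometric indices, and waist and hip are measured by tape. Section *Intervention* has weekly diet-compliance calls, and the research team is in weekly contact with participants. Knowledge of the arm could affect that contact and those measurements.
- **Concealment of future assignments.** Someone who knows the parity key and sees the next bottle number can foresee the next allocation.

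The parity rule is also left unreconciled with the block list and envelopes. It could be a labelling step applied after the list is made, or a second allocation device. The text does not say which.

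**Working it through.** **Inputs.** The parity rule, the numbered bottles and the replacement of A or B by codes come from *Blinding and randomization of participants*. The same section gives 25 per group, so 2 × 25 = 50 participants. The plan gives no figure of its own on this point, so there is none to reproduce.

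**Step 1: what one known allocation reveals under parity.** Only two mappings exist: even = SB, or odd = SB. Before any disclosure each has probability 1/2. One participant with known number and known arm settles the mapping, so 50 − 1 = 49 of the other 49 arms follow, and so does the arm of every bottle not yet issued.

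**Step 2: the same disclosure with unique, uninformative codes.** With 25 per arm and ignoring blocks and strata, another participant is in the opposite arm with probability 25/49 = 51% and in the same arm with probability 24/49 = 49%. Blocking shifts these odds for others in the same block. It does not carry over to other blocks.

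**Step 3: inference without a leak.** Under parity, weak clues pool, because each guess about a participant is also a guess about the one mapping. Let each of *k* independent guesses be right with probability *q*. The majority is right with probability Σ C(*k*, *j*) *q*^*j* (1 − *q*)^(*k* − *j*), summed from *j* = (*k* + 1)/2 to *k*. Neither *q* nor *k* is in the document; both are assumptions, shown over a range:

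| Assumed *q* | *k* = 5 | *k* = 25 |
|---|---|---|
| 0.55 | 0.59 | 0.69 |
| 0.60 | 0.68 | 0.85 |
| 0.70 | 0.84 | 0.98 |

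With unique codes, a guess bears on its own participant only and cannot be pooled in this way.

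**Step 4: do the stated safeguards break the chain?**

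| Safeguard | What it does | What it leaves open |
|---|---|---|
| Specific codes | Replace the group letters | Not said to be unique per participant, or to hide the number; two group-level codes would have the same weakness |
| Individual unblinding envelopes with an uninvolved consultant | Make a leak less likely | The consequence of a leak, if one occurs |
| Rule against recording or telling the revealed code | Makes a leak less likely | The same |
| Matching bottles and capsules | Hide the product | A number on the label |

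Capsules are handed out every 30 days and returned ones are counted (*Intervention*), so there is more than one occasion on which a label could be read.

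**The case against.** The strongest reply is that the premise is not stated. The wording is loose and allows a second reading: parity may be the third person's internal device for linking numbers to arms, with blinded people seeing only the specific codes. The sentence on codes gives maintaining the blind as its purpose, which supports that reading. If the codes are unique per participant and replace the numbers on the labels, the leak closes. This part of the reply stands, and it makes the point conditional. It does not remove the point, because the text never says that the codes have those properties.

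A reader might infer three stronger things that the document does not support:

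- **That one emergency unblinding discloses every arm to the trial team.** Under the stated procedure the consultant opens the envelope and may not record or tell the code, so the disclosure should not reach blinded staff. A breach would be needed.
- **That the same people counsel participants and take all the measurements.** The document does not say who measures at weeks 0 and 8, and it names outcome assessors separately from researchers. Appetite is self-completed on a visual analog scale and is not among the listed primary or secondary outcomes.
- **That gastro-intestinal symptoms will reveal the arm.** They are described as possible and temporary, the section *Adverse effects, safety, and data monitoring* says no side effect is known at this dose, and no rates by arm are given. Clustering on one parity is a possible route, not a demonstrated one.

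The remaining primary outcomes (GLP-1 and gene expression) are laboratory assays and leave less room for assessor bias.

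**Conclusion.** The concern holds in conditional form. As written, the parity rule links the label to the arm, and nothing else in the section says that blinded people cannot see the number or that the codes are unique. If the number is visible, one leaked or correctly inferred allocation exposes the other 49 of 49 participants and all unissued bottles. With unique codes, it would leave others at about 51% against 49%.

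The 49 of 49 follows from the rule itself, given visibility. The pooled-guess figures (0.59 to 0.98) rest on assumed guess accuracy, an assumed number of guesses and independence, and are illustrative only. The document does not show that the triple blind failed. It shows a coding rule that makes the blind needlessly fragile, where a better rule costs almost nothing.

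**What to change.** 1. Delete the even/odd rule.
2. Have the third person give each position on the stratified block list a unique random bottle code unrelated to arm, with no parity or other digit pattern. Only the third person and the unblinding consultant hold the key.
3. State in one sentence how the block list, envelopes and bottle codes fit together, and that the code is all a blinded person sees.
4. Apply this to any bottles not yet issued.
5. If bottles were already issued under parity coding, say so, state who could see the numbers, and qualify the triple-blind claim to match.

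**Cost.** One revised paragraph and minor relabelling, with care to avoid mix-ups. The randomisation list, sample size and analysis do not change. *Trial status* expected recruitment to run from June to November 2021, although it also calls it underway, so relabelling may reach few bottles or none. In that case item 5 is the part that matters.
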